#### Phase IV

All outcomes assessed via qualitative interviews:Experiences of using desks, including factors perceived as affecting desk use, issues with desk use (contextual, practical, emotive or others) and adverse consequences (work, health or otherwise related)Experiences of other intervention componentsCompany representatives’ perceptions of using sit-stand desksAcceptability of interventionAcceptability of assessments and burdenAcceptability of study procedures

#### Other measures

Proportion of participants dropping out between phases

#### Data analysis

The main analysis of this study will include descriptive statistics of feasibility and acceptability outcomes, including recruitment and attrition rates. We will also calculate differences between the average change from baseline in energy expenditure and sitting time between the intervention and control groups to estimate possible effect sizes from which to power the main trial.

Analysis of the anonymised data gathered through the semi-structured interviews will be conducted following the principles of the Framework method [41].

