### Aim and objectives

The aim of the current study is to assess the feasibility of conducting a randomised controlled trial of the impact of sit-stand desks at work on energy expenditure and sedentary time. The specific objectives of the study are to:Assess the feasibility of recruiting eligible participants into the trial, by estimating and describing:(i)The proportion of eligible participants who are interested in taking part in the trial(ii)The baseline characteristics of eligible participants who are interested in participating in the trial, to judge the likelihood of recruiting a sample varied in the potential effect modifiers of interest (BMI, SES, age, gender)(iii)The expected recruitment rate(iv)The number of recruitment sites (organisations) needed to achieve the target sample size for the main trial
Estimate the number of desk mounts and full desks needed for the main trial, by describing:(i)The proportion of eligible participants preferring desk mounts vs full desks(ii)The proportion of eligible participants with workspaces that permit installation of their desk preference
Explore people’s preference regarding the location for the baseline and follow-up assessments (home vs workplace vs clinical research facility)Assess the feasibility and practicalities associated with delivering the intervention (i.e. installing the sit-stand desks)Explore the circumstances under which desks are used in standing mode and the factors that affect desk useEstimate retention and loss to follow-up ratesExplore the acceptability of the interventionExplore the acceptability of the outcome assessments and study proceduresAssess the variability of outcomes, to inform sample size calculations for the planned trial

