### Sample size

No formal sample size calculations are produced for this feasibility study. Sample sizes for each phase (see Fig. 1) are chosen based on resources. However, it is possible to determine the precision with which certain parameters can be estimated with the sample sizes chosen for each of the study phases.

To achieve the target of 500 individuals completing phase I, the survey will be circulated to approximately 1400 individuals. Although in organisational research the average response rate from individual respondents is 53 %, we have based our estimate on the conservative expected rate of 35 %, which is the average survey response rate for organisational respondents [77–79].

Based on the average interest rates reported in previous studies assessing the impact of sit-stand desks on sitting time, the expected proportion of participants interested in taking part in a trial of sit-stand desks at work is 37 %. With 500 participants, the 95 % confidence intervals around an estimate of 37 % would be from 33 to 41 %.

Based on the average recruitment rates reported in previous studies assessing the impact of sit-stand desks on sitting time, the expected recruitment rate is 33 %. With 500 participants, the 95 % confidence intervals around an estimate of 33 % would be from 29 to 37 %.

The average attrition rate between baseline and follow-up reported in previous studies assessing the impact of sit-stand desks is 10 %. With 20 participants, the 95 % confidence intervals around an estimate of 10 % would be from 2 to 33 %. The maximum attrition rate reported in previous relevant studies is 14 %. With 20 participants, the 95 % confidence intervals around an estimate of 14 % would be from 3.5 to 38 %.

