#### Assessments

Of those randomised during phase II, 10 participants, five from the interventions group and five from the waiting list control group, will complete the baseline and follow-up assessments.

Based on their preference of location, participants will be visited by a researcher at their home, or place of work, or invited into a clinical research facility for all baseline assessments to be made prior to randomisation. The measurements will include anthropometric (height, weight, fat mass, fat-free mass, waist and hip circumference) and blood pressure measurements and collection of a blood sample to measure total cholesterol, HDL, triglycerides and HbA1C. Participants will also be asked to complete a questionnaire to assess musculoskeletal discomfort and other health symptoms, ability to work, presenteeism, absenteeism and job satisfaction, quality of life and domain-specific sedentary behaviour.

They will also be fitted with a combined heart rate and movement sensor (Actiheart) on the chest and asked to complete either a stepping test, if assessed at home or work, or a treadmill test if assessed in the clinical research facility. They will also be fitted with a thigh-based accelerometer (activPAL) to measure baseline sitting standing and stepping time and sitting and standing patterns. Both devices will be worn for 24 h/day for seven consecutive days. Participants will also be required to complete a brief daily log with wake and sleep times, work hours and any device removal, as well as their food intake. Participants will receive instructions on devices and log use. Devices and logs will be collected by research staff at the end of the 7-day period.

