#### Phase III

Practicalities of delivering the intervention, assessed by recording:° The time lapse between ordering the desks from the manufacturer and their delivery° Any permissions needed to install each desk type° The feasibility of training research staff to install desks° The feasibility of one person (a trained research assistant) installing each desk without help° The amount of time needed to install each desk° Any problems associated with delivering the desks to participants° Any problems installing each desk type° The practicalities associated with removing existing desks (applicable only when using full desks)
Circumstances and factors affecting desk use assessed via direct observations and diaries/logsProportion of participants dropping out between randomisation and the 3-month follow-upTrial-related outcomes, assessed at baseline (before randomisation) and at 3-month follow-up:° Physical activity energy expenditure estimated via Actiheart^3^ monitors° Sedentary behaviour measured using activPAL inclinometers^4^:Sitting time during (a) working hours (workplace sitting time) and (b) all waking hours (total sitting time)Sitting patterns (number of sit-to-stand transitions; sitting time accrued in prolonged bouts (≥30 min)) during (a) working hours (workplace sitting patterns) and (b) all waking hours (total sitting patterns)
° Cardio-metabolic related outcomes:BMI calculated from weight and heightWeight measured using a scaleHeight measured using a stadiometerFat mass and fat-free mass measured via a spectroscopy deviceBlood pressure, measured via an electronic monitorWaist-hip circumference measured using a tape measurePlasma total cholesterol, HDL, triglycerides and HbA1C, measured via non-fasting blood tests
° Musculoskeletal discomfort measured using the Nordic Musculoskeletal Questionnaire [80]° Ability to work, work productivity, presenteeism, absenteeism and job satisfaction measured using the Work ability index [81], the Stanford presenteeism scale [82] and Measure of job satisfaction [83]° Domain-specific sedentary behaviour measured using the SIT-Q-7d, a domain-specific last-7-day sedentary behaviour questionnaire [84]° Health symptoms, including neck pain, headache, back pain, fatigue, eye strain and loss of concentration, measured using a checklist° Health-related quality of life measured using the Euro-Quality of Life 5 (EQ-5D-5L) [85]° Food and drink consumption measured using a daily food log

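### The 5 v 5 effect estimate is an unadjusted difference in mean change; a baseline-adjusted estimate, with the SDs and the correlation, should be reported beside it (cheap improvement, low severity)

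*Protocol article*

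**What the plan says.** The Data analysis section of the protocol article makes descriptive statistics of feasibility and acceptability the main analysis. It then adds a calculation of "differences between the average change from baseline in energy expenditure and sitting time between the intervention and control groups", with the stated purpose "to estimate possible effect sizes from which to power the main trial". No baseline-adjusted model is mentioned.

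The Assessments section limits these measurements to "10 participants, five from the interventions group and five from the waiting list control group". Under Outcomes and measures, Phase III, the outcomes are "assessed at baseline (before randomisation) and at 3-month follow-up", so each measured person has a pre-randomisation value that could serve as a covariate. One listed objective is to assess "the variability of outcomes, to inform sample size calculations for the planned trial", without naming which SD is meant. The Sample size section states "No formal sample size calculations are produced for this feasibility study". The article gives no SD, effect size or correlation for energy expenditure or sitting time, and no analysis model for the main trial.

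**The concern.** With five per arm, an appreciable chance difference in baseline means is likely. A change score subtracts the whole of that difference, although only a fraction r of it is expected to persist to follow-up when the SDs are equal. The realised contrast is therefore pushed the opposite way to the imbalance (regression to the mean). The team will have one realised sample and intends to take an effect size from it.

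The second matter is what gets passed on. If only a difference in mean change and its SD are reported, a main trial that adjusts for baseline would lack its matching variability input and could be made larger than it needs to be.

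**Working it through.** **The plan's own figures.** The only precision figures in the article are 95% intervals for proportions. They reproduce as printed: 37% of 500 gives 32.8 to 41.2% and 33% of 500 gives 28.9 to 37.1% (Wald); 10% of 20 gives 1.75 to 33.1% and 14% of 20 gives 3.5 to 37.7% (Wilson with continuity correction). There is no figure to reproduce for the change-score comparison.

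**Inputs.** From the article: n = 5 per arm, N = 10, one baseline and one follow-up value each. Assumed: equal SDs (s = 1) at both times, normal outcomes, and r from 0.3 to 0.9.

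**1. Size of chance imbalance.** SE of the baseline difference = √(2/5) = 0.63 SD. The probability that it exceeds 0.5 SD in either direction is 0.43; that it exceeds 1 SD, 0.11.

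**2. Effect on the contrast.** Given a baseline difference d, the change-score contrast is shifted by −(1 − r)d. For d = 0.63 (one SE):
- r = 0.3: 0.7 × 0.63 = 0.44 SD
- r = 0.5: 0.5 × 0.63 = 0.32 SD
- r = 0.7: 0.3 × 0.63 = 0.19 SD

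In 200,000 simulated 5 v 5 trials, for imbalances of about 1 SD, the mean shift was −0.68, −0.48, −0.29 and −0.19 SD at r = 0.3, 0.5, 0.7 and 0.8. The adjusted estimate had a shift of about zero at each.

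**3. Precision over all randomisations.** Variance of the change-score difference = 2(1 − r) × 2/n. Variance of the adjusted difference = (1 − r²) × 2/n × (N − 3)/(N − 4), where the last factor, 7/6, is the cost of estimating the slope. The ratio, adjusted to change, is (1 + r)/2 × 7/6.

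| r | SE, change | SE, adjusted | Variance ratio |
|---|---|---|---|
| 0.3 | 0.748 | 0.652 | 0.76 |
| 0.5 | 0.632 | 0.592 | 0.88 |
| 0.6 | 0.566 | 0.547 | 0.93 |
| 0.7 | 0.490 | 0.488 | 0.99 |
| 0.8 | 0.400 | 0.410 | 1.05 |
| 0.9 | 0.283 | 0.298 | 1.11 |

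The SEs are equal at r = 2 × 6/7 − 1 = 0.71. Allowing for 7 rather than 8 degrees of freedom (t = 2.365 v 2.306), the interval widths are equal at r = 2 × (6/7) × (2.306/2.365)² − 1 = 0.63. Simulated mean widths put this nearer 0.67. If one of the ten is lost, as the article's 10% attrition would imply, the factor becomes 6/5 and the SE break-even is 2 × 5/6 − 1 = 0.67.

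**4. Consequence for sizing, if the main trial adjusts for baseline.** Change variance over residual variance = 2(1 − r)/(1 − r²) = 2/(1 + r). Sizing on the change SD would inflate n by 33% at r = 0.5 and 18% at r = 0.7. As an illustration, with an assumed effect of 0.5 SD, 80% power and two-sided 5%, n per arm by change SD and by residual SD is 88 v 58 (r = 0.3), 63 v 48 (0.5) and 38 v 33 (0.7).

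**5. How well these inputs are known.** Chi-square limits for an SD are 0.66 to 2.04 times the estimate on 7 df and 0.68 to 1.92 times on 8 df. Squared, the implied main-trial n runs from 0.44 to 4.1 times and from 0.46 to 3.7 times. The 95% half-width of the effect is 2.306 × 0.632 = 1.46 change SDs, or 2.365 × √(0.4 × 7/6) = 1.62 residual SDs. At r = 0.5 these are 1.46 and 1.62 × 0.866 = 1.40 outcome SDs.

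**The case against.** The strongest reply is that nothing here is wrong. Under randomisation the difference in mean change is unbiased on average, it is a secondary calculation in a feasibility study, and covariate detail is often left to a fuller document than an article. Regressing change on group and baseline gives the same treatment estimate as regressing follow-up on them, so the wording does not expressly rule out adjustment. Most of this stands and is why the severity is low. But the article does name an estimator and its use, and on a plain reading a difference between average changes is unadjusted.

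A reader might infer three stronger points that the documents do not support:
- *Adjustment is simply better here.* At N = 10 it loses precision above r of about 0.63 to 0.71, and the article gives no r.
- *The residual SD is what the main trial needs.* The main trial's model is not stated.
- *The main trial will be oversized by 18 to 33%.* That needs it to be sized on the change SD and then analysed with baseline adjustment, and the article says neither. If the raw SDs were reported with the change SD, the correlation could be recovered from them.

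It is also fair to say that the imprecision in step 5 swamps an 18 to 33% difference in n. The correlation is no better known: at n = 10 and an observed r of 0.5, the Fisher interval is about −0.19 to 0.86. This argues for reporting intervals and for caution about the effect estimate. It does not argue for leaving the quantities out.

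**Conclusion.** The point holds as a cheap improvement of low severity. The planned change-score contrast is legitimate, but in this one 5 v 5 sample it is exposed to chance baseline imbalance: about 0.32 SD for a one-SE imbalance at r = 0.5, and 0.19 to 0.44 SD for r between 0.7 and 0.3. An adjusted estimate removes that conditional bias using data already collected. It does not reliably narrow the interval, and it does not make an effect estimate from ten people fit to power a trial on its own.

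The figures rest on assumed values of r and on equal SDs at the two times. With unequal SDs the shift depends on the slope of follow-up on baseline rather than on r, and it vanishes if that slope is 1.

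**What to change.** In the Data analysis section, for energy expenditure and sitting time:
- Report the baseline-adjusted difference (linear model of follow-up value on group and baseline value) with its 95% CI, alongside the change-score difference.
- Report the raw baseline and follow-up SDs, the change SD, the residual SD and the baseline/follow-up correlation, each with a CI. This also gives the variability objective a definite meaning.
- State that, if the main trial is analysed with baseline adjustment, it will be sized on the residual SD using a conservative (low) correlation.
- State that SDs on 7 to 8 df leave the implied main-trial n uncertain by a factor of about 0.4 to 4, and that the 5 v 5 effect estimate will not by itself set the main-trial effect.

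Cost: one degree of freedom in the adjusted model (7 instead of 8), a few lines of wording and a little more analysis. No new data, visits or participants are needed.

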## Discussion

The time spent in sedentary behaviour is rapidly increasing in middle- and high-income countries and is expected to continue to do so without intervention [23]. Given the health implications of prolonged and uninterrupted sitting, this creates a huge public health problem. Reducing and/or breaking up sitting time at work could substantially attenuate the risk of disease among office workers [19, 20], who are sedentary a large proportion of their day. Given that office workers are one of the largest occupational groups in high-income countries [37, 38], reducing their sedentary behaviour could have important public health implications, making them an important target for intervention.

Most existing interventions to reduce workplace sitting time have focused on changes to the physical environment of workplaces, policy changes and information and counselling [67]. Although strategies falling under the latter two categories have produced inconsistent effects, there is some evidence to suggest that those involving workplace physical changes and specifically the use of sit-stand desks are effective [67]. However, the quality of this evidence is low [41, 67, 68] and key uncertainties remain regarding the use of sit-stand desks at work, including their impact on energy expenditure (in and outside of work) and sitting time in the longer term.

The current feasibility study is designed to finalise the design and conduct of a future, full-scale trial to assess the impact of sit-stand desks at work on energy expenditure (in and outside of work) and sitting time in the short and longer term, in a robust design using objective, reliable and valid measures of energy expenditure and sitting time. Its primary purpose is to address key design uncertainties for the trial, including the feasibility of recruiting eligible participants, their preferences for full sit-stand desks vs desk mounts, the suitability of workplaces for installing each desk type, the practicalities associated with delivering and installing the desks, and to explore the options regarding the location for conducting the assessments (home vs work vs clinical research facility). The qualitative component of the study will allow for exploration of any issues surrounding the acceptability of sit-stand desks from the perspective of the users, as well as of the employers, and of the factors (contextual and personal) that influence desk use. It will also allow for exploration of the acceptability of the study procedures and assessment methods.

The full trial, the design of which the proposed feasibility study aims to clarify, is expected to extend current knowledge regarding the effectiveness of sit-stand desks at work in reducing sedentary behaviour. By focusing on questions regarding the desks’ impact on energy expenditure at work and outside, as well as short and longer term sitting time, using a rigorous design, including mixed methods and robust measures, the trial will provide essential information regarding the intervention’s likely cardio-metabolic health impacts in the short and longer term, which are currently lacking [70]. The findings from this trial are, therefore, expected to inform discussions regarding the potential of sit-stand desks at work to improve outcomes related to the development of risk factors for diseases arising from prolonged sitting.
